#### Stratification of participants

The Friedreich’s Ataxia Rating Scale (FARS) functional staging for ataxia scale [51], will be used to stratify participants with FRDA into disease stage subgroups as outlined in Table 2. At the time of enrolment, we aim to have 55% of participants in FARS functional stages 0–2, 35% in the functional stages 3–4 and 10% in functional stage 5. Individuals in stage 6 will not be enrolled. This will create a cohort largely representative of those earlier in the disease process. Those earlier in the course of disease, particularly those who are still ambulant, progress at a much faster rate [27, 52, 53], hence detecting progression through proposed biomarkers in this cohort may be more efficient.

**Table 2 pone.0269649.t002:** The FARS Functional Staging for Ataxia scale describing the clinical presentation at each stage.

Friedreich’s Ataxia Rating Scale Functional Staging for Ataxia Scale	
Functional staging	Clinical presentation
Stage 0	Normal
Stage 1	Minimal signs detected by physician during screening. Can run or jump without loss of balance. No disability
Stage 2	Symptoms present, recognized by patient, but still mild. Cannot run or jump without losing balance. The patient is physically capable of leading an independent life, but daily activities may be somewhat restricted. Minimal disability
Stage 3	Symptoms are overt and significant. Requires regular or periodic holding onto wall/furniture or use of a cane for stability and walking. Mild disability. (Note: many patients postpone obtaining a cane by avoiding open spaces and walking with the aid of walls/ people etc. These patients are graded as stage 3.0)
Stage 4	Walking requires a walker, Canadian crutches or two canes and or other aids such as walking dogs. Can perform several activities of daily living. Moderate disability
Stage 5	Confined but can navigate a wheelchair. Can perform some activities of daily living that do not require standing or walking. Severe disability
Stage 6	Confined to wheelchair or bed with total dependency for all activities of daily living. Total disability

#### Study visits

Each study visit will include a clinical assessment (most items applicable to individuals with FRDA only), cognitive and mood assessments, collection of demographic and medical information, MRI of the brain and spinal cord, and collection of a blood sample. The schedule followed by each participant is dependent on their age group (Fig 1).

**Fig 1 pone.0269649.g001:**
[figure not shown]
Summary of TRACK-FA study procedures according to participant age. The testing schedule varies according to age. All participants will also undergo a speech assessment, whilst all FRDA participants will undergo additional clinical testing.

*Collection of medical and demographic information*. Medical history specific to FRDA will be taken in the enrolment session for all participants with FRDA. The following information will be collected: the length of *FXN* GAA repeat expansions on the smaller (GAA1) and larger (GAA2) allele, the type of mutation detected, age of symptom onset including first symptom, disease duration, presence of diabetes and medical information pertaining to nervous system disorders (apart from FRDA), heart conditions, vision impairments, skeletal abnormalities (scoliosis and foot deformities), hearing conditions, bowel and bladder conditions, presence of inflammatory diseases, details on concurrent trial participation and COVID-19 status.

The following information will be collected for all participants: height and weight (used to calculate body mass index (BMI), and medications (prescription/non-prescription).

*MRI scanning to assess primary outcomes*. All participants will undergo brain and (cervical) spinal cord imaging procedures lying supine in a three tesla (3T) MRI scanner (Siemens Skyra, Siemens Prisma or Philips Ingenia). Significant effort has been made to ensure harmonisation of MR protocols across all the sites with vigorous testing of the imaging sequences prior to the commencement of the study. The inclusion of QSM, diffusion MRI and MRS in the procedure allows for the quantification of iron accumulation, microstructural and neurochemical profile of areas pertinent to disease pathology [39], potentially providing further insights into neuronal damage and gliosis associated with the neurodegenerative nature of this disease [32].

Depending on age, one of two MRI protocols will be used: the first protocol, approximately 90 minutes long, will be used in all participants aged >10 years. The second, approximately 30 minutes long and designed to be less taxing for younger children, will be used in the 5–10 years age group. The young child protocol only includes anatomical scans (brain and spinal cord), but no diffusion MRI, brain QSM, or spinal cord MRS. Brain T1, T2 and diffusion acquisitions are based on those used in the Human Connectome Project [36]. Brain QSM acquisition was optimised to provide excellent image quality and contrast with 0.9 isotropic resolution. The spinal cord T2, diffusion and MEDIC acquisitions are based on a recently published spinal cord protocol [37]. The spinal cord MRS is based on a semi-LASER sequence developed at the University of Minnesota [54], with addition of metabolic cycling. The specific MR sequences, acquisition time, and key parameters for each sequence are outlined below in Table 3. These sequences will be used to acquire the outcome measures provided in Table 4.

**Table 3 pone.0269649.t003:** TRACK-FA protocol used to obtain cervical spinal cord and brain MRI data.

Data	Sequence	Resolution	Main parameters	Acq. time
Spine T2	3D SPACE	0.8 mm iso	TE 120 ms, TR 1500ms, iPAT 3	4’02”
Spine MRS battery (includes power calibration and shimming)	semiLASER (CMRR)	8 x 6 x 33 mm	TE 30 ms, TR 2500 ms, NA 160	8’10””
Spine diffusion	2D SE-EPI with ZOOMit	0.9 x 0.9 x 5mm	TE 61 ms (Skyra 92ms), TR 620 ms (Skyra 680 ms), 5 concatenations, 30 dirs, b = 800, 5 b0 On Skyra, NT = 2 for diffusion weighted volumes (b = 800)	4‘(AP) + 1’ (PA) (b0 only) (with pulse trigger) On Skyra these times are nearly doubled)
Spine MEDIC	2D multi-echo	0.5 x 0.5 x 5mm	TE 14 ms, TR 600 ms, NA 2, 3 echoes, iPAT 2	4’45”
Brain T1	3D MPRAGE	0.8 mm iso	TE 2.2ms, TR 2400 ms, TI 1000 ms, iPAT 2	6’38”
Brain T2	3D SPACE	0.8 mm iso	TE 563ms, TR 3200 ms, iPAT 2	5’57”
Brain diffusion	Multiband EPI (CMRR)	1.5 mm iso (Skyra 1.7 mm iso)	TE 89ms (Skyra 102 ms), TR 3230 ms (Skyra 3366 ms), MB 4, 197 dirs, 2 shells, b = 1500/3000, 6 b0	5’37” (AP) + 5’37” (PA)
				Skyra 5’52” (AP) + 5’52” (PA)
Brain QSM	3D GRE	0.9 mm iso	TE1/TE2/TE3/TE4 = 3.7/9.7/15.8/21.9 ms, TR 27ms, iPAT 2	7’22”

* For participants 10 years old and younger, only anatomical data (highlighted in grey) are collected.

** The times above are data acquisition times for each sequence and do not include time for adjustments (e.g., scout images, shimming, power calibration) and ROI planning.

**Table 4 pone.0269649.t004:** The brain regions, modalities, and outcome measures for the TRACK-FA MRI protocol.

Region	Modality	Outcome measure
Brain	Structural MRI (Brain morphometry)	Total brain volume
		Total white matter volume
		Total grey matter volume
Brain	Structural MRI (Cerebellum morphometry)	Total cerebellar volume
		Superior cerebellar peduncles volume
Brain	Quantitative susceptibility mapping (cerebellum only)	Iron concentration in the dentate nuclei*
		Volume of the dentate nuclei*
Brain	Diffusion MRI	Superior cerebellar peduncle fractional anisotropy*
		Superior cerebellar peduncle mean diffusivity*
		Superior cerebellar peduncle radial diffusivity*
		Superior cerebellar peduncle axial diffusivity*
Spinal cord	Structural MRI (morphometry) (Values extracted from the spine T2 image)	Cross sectional area of the cervical spinal cord, averaged over two C2-C3
Spinal cord	Diffusion MRI	Total White matter changes in fractional anisotropy*, mean diffusivity*, radial diffusivity*, axial diffusivity*
Spinal cord	Magnetic resonance spectroscopy (Voxel positioned over C4-C5)	Total N-acetyl-aspartate (tNAA)/myo-inositol (mIns) ratio*

(*) only undertaken for participants > 10 years of age.

*Clinical measures to assess secondary outcomes*. Individuals with FRDA will undergo assessments using neurologic scales and functional measures outlined in Table 5. Additionally, all participants enrolled will undergo speech assessments. The speech assessment is conducted using the REDENLAB software [58], consisting of an adult battery (for those aged ≥ 18 years) and a paediatric battery (aged 5–17 years).

**Table 5 pone.0269649.t005:** Neurologic and functional measures completed by TRACK-FA participants.

Assessment	Description
FARS Staging for Ataxia Scale	This assessment indicates the impact of FRDA on function.
mFARS neurological exam (FARS subscale)	The mFARS comprises four subscales (bulbar, upper limb coordination, lower limb coordination, and upright stability) and has a maximum score of 93 [34]
FARS Activities of Daily Living (ADL)	The ADL, assessed in a structured guided interview setting, is a component of the FARS and aims to quantify essential and routine aspects of self-care, The ADL comprises 9 questions and has a maximum score of 36 [51]
Scale for Assessment and Rating of Ataxia (SARA)	The SARA is a semi-quantitative assessment of ataxia, measuring ataxia of upper limb, lower limb, gait, balance and speech. It has eight items, with the total score ranging from zero (no ataxia) to 40 (severe ataxia) [55]
9- Hole-Peg test (9HPT)	This test examines finger dexterity and involves placing and removing nine pegs in a pegboard in the quickest possible time. The 9HPT has high intra- and inter-rater reliability and is the most commonly used measure of upper limb function in FRDA [56]
Low-Contrast Sloan Letter Chart (LCSLC) testing	Contrast letter acuity testing for vision will be performed using the low-contrast Sloan letter charts (LCSLC–Precision Vision, La Salle, IL) [57]. Binocular LCSLC measurements will be obtained at 2 meters for each of three contrast levels (100%—equivalent to high-contrast visual acuity, 2.5%, and 1.25% contrast levels)
*Measures of Dysarthria	Dysarthria is measured using speech testing. The specific speech testing software used is the REDENLAB software [58] consisting of an adult and paediatric battery

*Clinical assessments undertaken by both individuals with FRDA and control participants.

*Cognitive and mood assessments to assess secondary outcomes*. Individuals with FRDA and control participants will undergo a range of cognitive and mood assessments for the TRACK-FA study. These assessments have been outlined in Table 6. Paediatric participants aged < 8 years will not be required to undergo measures of cognition or mood.

**Table 6 pone.0269649.t006:** The cognitive and mood assessments completed by TRACK-FA participants.

Assessment	Description
Cerebellar Cognitive Affective/Schmahmann Syndrome Scale (CCAS)	The CCAS is a 10-item scale assessing the executive, visual spatial and linguistic components of cognitive control and affect [59]. This assessment will be only completed by those in the ≥18 age group
Hayling Sentence Completion Test (HSCT)/ Junior HSCT	The HSCT will be completed by those in the ≥ 18 age group, while the Junior HSCT [60] will be administered to the 11–17 and 8–10 age groups. The HSCT is a measure of response initiation and suppression [60–62], and has demonstrated sensitivity to detect cognitive deficits in FRDA [63]
The Hospital Anxiety and Depression Scale (HADS)/ Revised Children’s Anxiety and Depression Scale (RCADS)	The anxiety and depression subscales are valid measures for severity of emotional disorder [64] with specific insights into variables such as: separation anxiety disorder, social phobia, generalized anxiety disorder, panic disorder, obsessive compulsive disorder, and major depressive disorder [65]. The Revised Children’s Anxiety and Depression Scale (RCADS) [66] will be completed by those in the 11–17 and 8–10 age groups

*Blood collection to assess exploratory outcomes*. A blood sample will be collected from each participant by a certified blood collection professional. The samples will be analysed for two proteins, frataxin and NFL, directly from whole blood, and from serum samples. At all visits, blood will be collected into serum separator tubes (SSTs), coagulated at ambient room temperature for 30 minutes and centrifuged. The samples will be shipped on dry ice at approximately six-monthly intervals to laboratories equipped to carry out frataxin and NFL analysis.

For those participants who do not have a record of GAA repeat sizing, extra blood will be drawn to conduct this analysis.

#### Adverse events

All adverse events will be captured by study sites and will be categorised according to the Standard Protocol Items: Recommendations for Interventional Trials (SPIRIT) guidelines [67]. Briefly, a Serious Adverse Event (SAE) is defined as an untoward or unexpected medical occurrence that results in death, is life-threatening, requires hospitalisation, results in persistent or significant disability or incapacity, or is a congenital anomaly or birth defect. Suspected Unexpected Serious Adverse Reactions (SUSAR) to medicinal products and other types of Adverse Events, including Non-Serious Adverse Events, Serious Adverse Events not related to TRACK-FA procedures, Non-Serious Adverse Reactions to medicinal products, and Serious Adverse Reactions to medicinal products will also be recorded. All Adverse Events, regardless of seriousness, and as related to TRACK-FA procedures, will be reported into a central repository, and reviewed at each quarterly meeting by the TRACK-FA Steering Committee. Sites will be obliged to report all Serious Adverse Events related to TRACK-FA procedures to the TRACK-FA Steering Committee within 24 hours via the PI/Safety Officer.

### Data analysis and statistical methods

#### Sample size calculation

The sample size required for this study was determined to satisfy a specified level of statistical power to detect a change in each measured parameter over the 24-month period. A minimum effect size of Cohen’s *d* = 0.3 was selected. The corresponding minimum number of participants (n) to detect such a change (*p*-value<0.05) with power greater than 0.80 was *n* = 70. We then doubled “n” to investigate changes in two sub cohorts: early stage and later stage yielding an *n* = 140. An important caveat is that the rate of change will be likely different in each sub-cohort, hence the power will be different in each sub-cohort. The final step was to add an additional 25% to the “*n*” to account for a possible 20% participant attrition over 24 months. An estimated recruitment size of *n* = 200 was selected. The TRACK-FA team includes experienced biostatisticians who will continue to advise on all statistical analyses throughout the study.

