### Objectives

**Objective 1:** To determine the longitudinal sensitivity of a range of candidate neuroimaging biomarkers in the brain and spinal cord and identify the biomarker(s) most sensitive to change over time in individuals with FRDA compared to control participants.

**Objective 2:** To determine differences in candidate neuroimaging biomarkers and their time of change between children and adults with FRDA, and matched controls.

**Objective 3:** To determine change over time in clinical severity, cognitive function, mood, speech, and fluid markers such as blood Neurofilament Light Chain (NFL) and frataxin in individuals with FRDA compared to controls.

**Objective 4:** To determine the relationship between imaging biomarkers and clinical, cognitive, mood, speech and blood markers of disease severity, including age of onset, GAA repeat size, disease symptoms and duration, disease severity, frataxin levels and NFL in individuals with FRDA.

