### Statistical analysis plan (SAP)

*MRI data analysis*. The MRI protocol includes the accumulation of multiple images using various MRI modalities as described in Table 3. The modalities are: brain structural MRI (T1 and T2 weighted), cerebellum structural MRI (using the same brain images but cerebellum-specific processing pipelines), brain diffusion MRI, brain QSM, spinal cord structural MRI, spinal cord diffusion MRI and spinal cord MRS. For each of these modalities, all data from all seven sites will be processed by a single site to ensure consistent data processing.

Brain morphometry (structural imaging) will be performed using FreeSurfer [68, 69] to determine brain total volume, total white matter volume and total grey matter volume. Cerebellum morphometry, performed using ACAPULCO [70], to determine the total cerebellar volume while SUIT [71] will be used to calculate the volume of left and right cerebellar peduncles. Brain DTI data will be analysed using FMRIB Software Library (FSL) [69, 72] to determine the fractional anisotropy (FAn) and mean, axial and radial diffusivity (MD, AD, RD) of the left and right SCP. Brain QSM data will be reconstructed using the JHU/KKI QSM Toolbox v3.0 from the MATLAB suite [73, 74], and the left and right dentate nucleus will be segmented manually [13].

Spinal cord morphometry will be performed on spine T2 images using the Spinal Cord Toolbox (SCT) [75]. Spinal cord DTI data will be analysed using FSL and SCT. Spine MRS data will be analysed using the linear combination of model spectra (LCModel) [76, 77].

Each of these analysis methods will be considered independently. The *p* values will be corrected for type 1 error inflation using Stepdown Bonferroni testing within each modality.

Statistical analysis.

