#### Assessing the longitudinal changes over time

The within-person longitudinal slopes across the multiple visits will be estimated using a mixed linear model in which the slope for each participant is treated as a random effect. Within this framework we will assess the significance of a fixed effect that captures the difference in mean slope for individuals with FRDA with respect to controls. Due to the participant demographic in this study the analysis of within person slopes can give an indication of how age of onset and disease stage/severity can influence the subsequent clinical changes that occur within the parameters of participant demography.

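### The sample-size calculation powers a change within FRDA, but the planned longitudinal tests compare FRDA with controls, for which the stated power above 0.80 does not hold at the expected retained numbers

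*Protocol article*

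**What the plan says.** Under Sample size calculation, the article says the study was sized "to detect a change in each measured parameter over the 24-month period". It chooses d = 0.3 as the minimum effect, p<0.05 and power above 0.80, and reports that the minimum sample "with power greater than 0.80 was *n* = 70". That figure is doubled "to investigate changes in two sub cohorts: early stage and later stage yielding an *n* = 140". A further 25% covers 20% attrition, and 200 is selected. The section does not name the test, its sidedness, the SD that scales d or any multiplicity allowance, and controls do not enter it. Study design nevertheless says that the total of 200 FRDA and 104 controls was informed by the power analysis.

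The analyses are framed differently. Objective 1 is to "identify the biomarker(s) most sensitive to change over time in individuals with FRDA compared to control participants". The longitudinal model tests "a fixed effect that captures the difference in mean slope for individuals with FRDA with respect to controls". The difference-in-difference section compares 12-month changes between the same two groups. The SAP section adds that the p "values will be corrected for type 1 error inflation using Stepdown Bonferroni testing within each modality".

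**The concern.** A calculation for one group's mean change answers a different question from a test of the difference between two groups' mean changes. The second has the sampling error of both groups, and here the control group is about half the size of the FRDA group. A power figure for the first therefore cannot be carried over to the second.

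The study is meant to pick out the markers most sensitive to change. A reader who trusts power above 0.80 at d = 0.3 would take a non-significant slope difference as evidence that a marker is insensitive, when the comparison may simply have had too little power.

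**Working it through.** **Inputs.** From Sample size calculation: d = 0.3, p<0.05, n = 70, 20% attrition. From Study design: 200 FRDA and 104 controls. From Stratification of participants: 55% in stages 0–2 and 45% in stages 3–5. From Table 4: four diffusion measures for the superior cerebellar peduncle and four for the cord. Assumed: 20% attrition in both groups, giving 200 × 0.8 = 160 and 104 × 0.8 ≈ 83; equal SD of change in both groups; and the same d applied to the FRDA-minus-control difference. Results are from the noncentral t; the normal approximations shown agree to about 0.01.

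**1. The plan's own figure, d on the SD of change.** One-sample noncentrality = d√n = 0.3 × √70 = 2.510.
- One-sided: Φ(2.510 − 1.645) = 0.81; t-based 0.80. This reproduces n = 70.
- Two-sided: Φ(2.510 − 1.960) = 0.71; t-based 0.70. Reaching 80% needs n = 90.

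**2. The plan's own figure, d on the between-person SD.** With visit-to-visit correlation r, the effect on the SD of change is 0.3/√(2(1 − r)). At r = 0.61 this is 0.3/√0.78 = 0.340, and a two-sided paired test with n = 70 has power 0.80. So n = 70 is also the two-sided minimum if r is about 0.61.

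**3. The onward arithmetic.** 70 × 2 = 140 and 140/0.8 = 175; choosing 200 adds margin. This chain is correct.

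**4. The planned contrast.** I approximate the slope test by a two-sample test on 24-month change, with noncentrality d√(n₁n₂/(n₁ + n₂)). For 160 v 83, √(13280/243) = 7.393.
- d = 0.3 on the SD of change: 0.3 × 7.393 = 2.218. Two-sided Φ(2.218 − 1.960) = 0.60; one-sided Φ(2.218 − 1.645) = 0.72, t-based 0.71.
- r = 0.61: 0.340 × 7.393 = 2.51. Two-sided power is 0.71.

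**5. Stage sub-cohorts.** Assume stages 0–2 against 3–5, so 160 × 0.55 = 88 and 160 × 0.45 = 72, each compared with all 83 controls. Two-sided power:

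| Contrast | d on SD of change | r = 0.61 |
|---|---|---|
| 160 v 83 | 0.60 | 0.71 |
| 88 v 83 | 0.50 | 0.60 |
| 72 v 83 | 0.46 | 0.55 |

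**6. Multiplicity.** With four measures the first step-down threshold is 0.05/4 = 0.0125. For 160 v 83 with d on the SD of change, power is 0.38.

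**7. Effect detectable with 80% two-sided power, on the SD of change.** (1.960 + 0.842)/7.393 = 0.38 overall. For 88 v 83, √(7304/171) = 6.536 gives 0.43; for 72 v 83, √(5976/155) = 6.209 gives 0.45.

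**8. No attrition.** 200 v 104 gives 0.70 two-sided and 0.80 one-sided with d on the SD of change, and 0.80 two-sided at r = 0.61.

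**The case against.** The strongest reply is that the scale of d is not stated, so no single power figure can be read off. That stands, and the results above are given on both scales. It can be pressed further: with d on the between-person SD, 160 v 83 has 0.81 power at r = 0.7 and 0.94 at r = 0.8. But at those correlations the two-sided minimum would be 55 and 37, not 70, so they do not fit the article's own figure.

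The planned model uses up to three visits and keeps participants who miss one, while my approximation drops 20% of each group outright. Some of that loss would be recovered. Full retention would bring the whole-cohort contrast to about 0.80 in two of the cases in step 8, but the article itself plans for 20% attrition.

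Several stronger readings are tempting and not supported:
- A reader might infer that n = 70 can come only from a one-sided test. Step 2 shows another route.
- A reader might infer that 80% power was promised for each sub-cohort against controls. The article speaks of changes in two sub-cohorts and names no such contrast. It does not define early and later stage, and it warns that power will differ between them, though because rates of change differ.
- A reader might think 104 arbitrary. It follows from the allocation ratios and age targets: 8 at 1:1 plus 192 at 2:1 gives 8 + 96 = 104. That is a source for the count, not a power basis.
- The 0.0125 threshold is a worst case. Cord area and spectroscopy have one measure each in Table 4 and need no correction within their modality.

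A condensed article may also leave the test and sidedness to the full protocol. The mismatch between what was sized and what will be tested does not depend on those details.

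**Conclusion.** The point holds as a mismatch of target, not as an arithmetic error. On both readings examined that reproduce n = 70, and with the planned 20% attrition in both groups, power for FRDA versus controls at d = 0.3 is below 0.80 in the full cohort: about 0.60 two-sided (0.71 one-sided) with d on the SD of change, and about 0.71 two-sided at a correlation of 0.61. If each stage sub-cohort is set against all 83 controls, it is about 0.46–0.50 and 0.55–0.60 respectively; that contrast and the 55/45 split are my assumptions. Change in controls in the same direction as in FRDA would make the difference, and so the power, smaller. The multiplicity correction reduces it further only where a modality has several measures.

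**What to change.** Keep the recruitment target. In Sample size calculation, state the test, the sidedness and the denominator of d behind n = 70, and label it a within-FRDA calculation. Then give power for the FRDA-versus-control slope contrast, on the study's own definition of d and at the expected retained numbers in both groups. Report it unadjusted and, where a modality has several measures, at the first step-down threshold. If d is on the SD of change, the unadjusted two-sided text would read: about 60% at d = 0.3, and 80% at d of about 0.38 overall and 0.43–0.45 per stage sub-cohort against all controls. If d is on the between-person SD, give the assumed visit-to-visit correlation as well.

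The cost is a rewritten paragraph and a less favourable stated power. No extra participants are needed.
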